## Abstract

**Background:**

The gap between the level of care recommended by evidence-based clinical practice guidelines and the actual care delivered to patients in practice has been well established. The Canadian Diabetes Association (CDA) created an implementation strategy to improve the implementation of its 2008 guidelines. This study will evaluate the impact of the strategy to improve cardiovascular disease (CVD) screening, prevention and treatment for people with diabetes.

**Design:**

A pragmatic cluster-randomized trial will be conducted to evaluate the CDA's CVD Toolkit. All family physicians in Ontario, Canada were randomly allocated to receive the Toolkit, which includes several printed educational materials targeting CVD screening, prevention and treatment, either in spring 2009 (intervention arm) or in spring 2010 (control arm). Randomization occurred at the level of the practice. Forty family physicians from each arm will be recruited to participate, and the medical records for 20 of their diabetic patients at high risk for CVD will be retrospectively reviewed. Outcome measures will be assessed for each patient between July 2009 and March 2010. The primary outcome will be that the patient is receiving a statin. Secondary outcomes will include 1) the receipt of an angiotensin converting enzyme inhibitor or angiotensin receptor blocker, 2) various intermediate measures (A1c, blood pressure, LDL-cholesterol, total-/HDL-cholesterol ratio, body mass index and waist circumference), and 3) clinical inertia (the failure to change therapy in response to an abnormal A1c, blood pressure or cholesterol reading). The analysis will be carried out using multilevel hierarchical logistic regression models to account for the clustered nature of the data. The group assignment will be a physician-level variable. In addition, a process evaluation study with six focus groups of family physicians will assess the acceptability of the CDA's Toolkit and will explore factors contributing to any change or lack of change in behaviour, from the perspectives of family physicians.

**Discussion:**

Printed educational materials for physicians have been shown to exert small-to-moderate changes in patient care. The CDA's CVD Toolkit is an example of a practice guideline implementation strategy that can be disseminated to a wide audience relatively inexpensively, and so demonstrating its effectiveness at improving diabetes care could have important consequences for guideline developers, policy makers and clinicians.

**Trial Registration:**

The trial is registered with http://www.clinicaltrials.gov, ID # NCT01026688

## Background

Diabetes is a common and serious chronic disease. Its prevalence is growing extremely rapidly, [1] and it is associated with impaired quality of life, premature mortality and significant economic costs [2-4]. One of the most important complications of diabetes is cardiovascular disease, as it accounts for about half of mortality in people with diabetes [3]. Fortunately, numerous randomized trials have shown that pharmacological and non-pharmacological approaches can reduce the risk of complications and morbidity for people with diabetes[5-8]. In particular, multi-faceted interventions that target behaviour modification, glycemia and cardiovascular risk factors substantially reduce cardiovascular events and mortality[9,10]. However, these approaches are complex, as they require management of the multiple risk factors that lead to complications. Clinical practice guidelines (such as those produced by the Canadian Diabetes Association [CDA]) can help health care providers and patients by synthesizing the enormous literature on diabetes management into specific recommendations for care. However, many studies have previously documented a gap between these recommendations and the actual care delivered to patients with diabetes in Canada[11-14]. The lack of impact of practice guidelines on actual clinical practice is not unique to diabetes -- studies in a variety of clinical areas have demonstrated this lack of effect[15-17]. Therefore, the implementation of evidence-based guideline recommendations in actual clinical practice needs to be improved.

For the 2008 update to the guidelines, the CDA formed a Dissemination and Implementation Committee to create a guideline implementation strategy[18]. The first component of this strategy was aimed at improving adherence with the recommendations for cardiovascular disease screening and treatment for people with diabetes, since this is the most important complication of the disease and since evidence-based preventive interventions are readily available. The strategy highlighted the identification of diabetic patients at high risk for cardiovascular events, treatment targets and methods for vascular protection, and the selection of patients and methods for coronary artery disease screening. The objective of this study is to evaluate the impact of the CDA's strategy to improve cardiovascular disease screening, prevention and treatment for people with diabetes.

## Methods and design

### Research design

We will conduct a pragmatic cluster-randomized controlled trial to evaluate the effectiveness of the CDA's physician-oriented cardiovascular disease toolkit to improve the management of cardiovascular risk factors for patients with diabetes. A "pragmatic attitude" to trial design leads to a different type of trial answering different questions than a traditional "explanatory attitude" to design[19,20]. Explanatory randomized controlled trials (RCTs) are conducted in well-resourced, idealized clinical settings with motivated clinicians focusing on the particular clinical problem, whereas pragmatic trials are conducted in real-world clinical care in a variety of practice settings. Patients in explanatory RCTs are very highly selected with stringent inclusion and exclusion criteria, whereas very little selection is done in pragmatic RCTs, leading to study populations that more closely reflect the range of patients seen in clinical practice. Interventions are strictly defined and enforced with close monitoring of adherence in explanatory RCTs, while they are applied more flexibly in pragmatic RCTs. Finally, explanatory RCTs usually have a single primary outcome that is the focus of the study, whereas pragmatic RCTs often examine a broad range of endpoints that may have relevance to patients, clinicians and decision makers. As a result of these differences, explanatory RCTs are useful to establish *efficacy *of treatment, whereas pragmatic RCTs can establish *effectiveness*. Pragmatic trials are thus particularly useful to evaluate strategies and population-based initiatives, such as the knowledge translation strategy being evaluated in this study.

### Intervention

The cardiovascular disease toolkit was packaged in a brightly-coloured box with CDA branding. (See Figure 1.) The contents included an introductory letter from the Chair of the practice guidelines' Dissemination and Implementation Committee; an eight page summary of selected sections of the practice guidelines targeted towards primary care physicians; a four page synopsis of the key guideline elements pertaining to cardiovascular disease risk; a small double-sided laminated card with a simplified algorithm for cardiovascular risk assessment, vascular protection strategies and screening for cardiovascular disease; and a pad of tear-off sheets for patients with a cardiovascular risk self-assessment tool and a list of recommended risk reduction strategies. (See Figure 2.)

**Figure 1 F1:**
[figure not shown]
**Packaging for the cardiovascular toolkit intervention**.

**Figure 2 F2:**
[figure not shown]
**Contents of the Toolkit included (left to right): a synopsis of the guideline elements pertaining to cardiovascular disease risk, a laminated card with a simplified algorithm for cardiovascular risk management, and a pad of tear-off sheets for patients with a cardiovascular risk self-assessment tool**.

In the intervention group, the Toolkit was mailed with the Spring 2009 edition of *Canadian Diabetes*, a newsletter from the CDA which provides practical information on diagnosis and treatment issues associated with diabetes that is sent quarterly to all primary care physicians in Canada. The content of this edition of the newsletter did not pertain to cardiovascular risk screening or treatment. Both the Toolkit and *Canadian Diabetes *were packaged together in a large mailing envelope. The control group received *Canadian Diabetes *alone in its usual shrink-wrap packaging, and will receive the Toolkit with the Spring 2010 edition of the newsletter.

### Allocation of participants

All family physicians in Ontario were randomized to either the intervention or control group using computer-generated randomization. Randomization occurred at the level of the practice based on the physicians' primary practice address recorded with the College of Physicians and Surgeons of Ontario, so that all physicians practicing at a single location were assigned to the same group. This was done to prevent contamination between physicians in group practices who may share information and resources. The randomization was stratified by health region.

In addition to the randomized distribution to family physicians in Ontario, the Toolkit was also distributed to all endocrinologists in Ontario, and to all family physicians and endocrinologists in all other Canadian provinces and territories in a non-randomized fashion. Endocrinologists will not directly form part of the study.

### Study participants

From the Toolkit's mailing lists, we will randomly select Ontario family physicians to approach about participating in a primary data abstraction study. Physicians will be contacted by fax with a brief synopsis of the study purpose and the planned data abstraction. They will be invited to accept or decline to participate by fax or telephone. Follow-up telephone calls will be made to physicians who do not respond. We will recruit 40 family physicians from each of the intervention and control arms. For practical reasons, the recruited physicians will practice within 150 km of the study centre, which incorporates both urban and rural areas. In order to increase the likelihood that the participating physicians are representative of typical practitioners and are not self-selected towards good performers with an interest in diabetes quality of care, the letter of invitation will not describe the study in detail or what data will be collected.

Individual patients with diabetes seeing each physician will be identified through the physician's billing records or electronic health records. We will randomly select from these records 20 diabetic patients per physician aged = 18 years who were seen in the office at least once between July 2009 and March 2010, and who fulfill the Clinical Practice Guidelines' definition of being at "high risk for CV events": [18]

• Men aged ≥ 45 years, women aged ≥ 50 years; or

• Men aged < 45 years and women < 50 years with at least one of the following:

• Macrovascular disease (silent myocardial infarction, or evidence of peripheral arterial, carotid arterial or cerebrovascular disease)

• Microvascular disease (nephropathy or retinopathy)

• Family history of premature coronary or cerebrovascular disease in a first-degree relative

• Extreme level of a single risk factor (LDL-C > 5.0 mmol/L, systolic BP > 180 mmHg)

• Duration of diabetes > 15 years with age > 30 years

Patients who were concomitantly seeing endocrinologists will not be specifically excluded from the study. Although such patients may be more likely to have received benefit from the Toolkit since all endocrinologists received the Toolkit in a non-randomized fashion, less than 18% of people with diabetes in Ontario see both endocrinologists and family physicians[21]. Any such patients would bias the results of the study towards the null.

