### Data collection and outcomes

Starting in the spring of 2010, we will perform a retrospective data abstraction from the paper charts and/or electronic health records in each physician's office. For each patient, demographic information (including date of birth, sex and postal code of home residence) and clinical information (including diabetes duration, comorbidities, family history and baseline drug utilization) will be collected. Outcome measures will be assessed for each patient for the period between July 2009 and March 2010. The primary outcome will be that the patient is receiving a statin (as determined by the record of a new prescription, the record of a prescription renewal, or a notation that the patient is taking a statin). This outcome is selected because as a process of care outcome, it is closely linked to physicians' behaviour and hence is more likely to change as a result of the intervention, and because no more than one-third of patients currently receive statins, [13,22,23] so there is substantial opportunity for improvement.

The other process outcome that will be evaluated is whether the patient is receiving a prescription for an angiotensin-converting enzyme inhibitor or angiotensin receptor blocker. In addition, the following intermediate outcomes will also be collected:

• A1c

• Blood pressure

• LDL-cholesterol

• Total-/HDL-cholesterol ratio

• Body mass index

• Waist circumference

When there are multiple measurements for these intermediate measures for a patient, the last one during the observation period will be used.

We will also measure "clinical inertia"[24]. For each A1c, blood pressure or LDL-cholesterol reading that is above the recommended clinical practice guideline target, we will determine whether, at the next patient visit, there is notation in the chart of a recommended change: the addition of a new medication, a dose change for an existing medication, a dietary or physical activity recommendation, etc.

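### Physicians accept or decline after allocation and after the Toolkit mailing, so acceptance could differ by arm; adjust the primary model for statin use before the mailing

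*Protocol article*

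**What the plan says.** Allocation is already complete in the protocol article (Allocation of participants): "All family physicians in Ontario were randomized to either the intervention or control group using computer-generated randomization". So is delivery (Intervention, text after Figure 2): "In the intervention group, the Toolkit was mailed with the Spring 2009 edition of" the association's newsletter. The control arm had the newsletter alone and "will receive the Toolkit with the Spring 2010 edition of the newsletter".

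The study sample is still to be formed (Study participants). From the mailing lists, "we will randomly select Ontario family physicians to approach about participating in a primary data abstraction study", and "They will be invited to accept or decline to participate by fax or telephone". Non-responders are telephoned. The target is set by arm: "We will recruit 40 family physicians from each of the intervention and control arms".

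To limit self-selection by physicians who perform well and care about diabetes quality, "the letter of invitation will not describe the study in detail or what data will be collected". The same section has the fax summarise the study's purpose and the planned abstraction, so how uninformative the approach will be is not entirely clear. Patients are selected at random within each physician, and the abstracting nurse is blinded to group (Data collection and outcomes).

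On baseline data, "clinical information (including diabetes duration, comorbidities, family history and baseline drug utilization) will be collected". Planned analyses specifies a multilevel logistic model with group as a physician-level variable and names no baseline covariate.

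**The concern.** Randomisation balances the arms over all Ontario family physicians. The analysis uses only those who agree to open their charts, and they decide after one arm has received a branded diabetes Toolkit and the other has not. If the Toolkit changes who agrees, for example by making physicians with an interest in diabetes more willing, the participants in the two arms may differ in statin prescribing for reasons unrelated to any Toolkit effect.

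The primary outcome is sensitive to this. It was chosen because it follows physician behaviour closely, so the mix of participating physicians feeds straight into it. With outcome data alone, a difference caused by who joined cannot be told apart from one caused by the Toolkit. It could mimic an effect or hide one.

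**Working it through.** **The plan's own figures.** Proposed sample size gives 408 per group before clustering, an intraclass correlation of 0.05 and 20 patients per physician.

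- VIF = 1 + 0.05 × (20 − 1) = 1.95.
- 408 × 1.95 = 795.6, so 796 per group. 796 / 20 = 39.8, so 40 physicians. This reproduces.
- The section states no base rate. 40% against 50%, two-sided 5%, 80% power, with continuity correction, gives 408. Those rates are an assumption and do not affect this point.

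**Inputs for the illustration.**

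- Statin rate of one-third in both arms: the upper limit in Data collection and outcomes.
- Intraclass correlation 0.05 and VIF 1.95: Proposed sample size.
- 40 physicians × 20 patients = 800 patients per arm.
- Difference between arms in the baseline prescribing of acceptors, in between-physician SDs: **assumed**, since the article gives no participation data.

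**Between-physician SD of the statin rate.** √(0.05 × 1/3 × 2/3) = 0.105, or 10.5 percentage points.

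**Standard error of the difference.** Effective patients per arm = 800 / 1.95 = 410. SE = √(2 × 1/3 × 2/3 / 410) = 0.0329, or about 3.3 points.

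**Rejection under no Toolkit effect.** For a spurious difference b, by normal approximation, P = Φ(b/SE − 1.96) + Φ(−b/SE − 1.96).

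| Assumed shift | b (points) | b/SE | P(reject) |
|---|---|---|---|
| 0 | 0 | 0 | 5% |
| 0.1 SD | 1.05 | 0.32 | Φ(−1.64) + Φ(−2.28) = 6% |
| 0.2 SD | 2.1 | 0.64 | Φ(−1.32) + Φ(−2.60) = 10% |
| 0.3 SD | 3.2 | 0.96 | Φ(−1.00) + Φ(−2.92) = 16% |

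Against the 10-point target difference, 2.1 and 3.2 points are 21% and 32%. By symmetry, a shift the other way would mask a true effect by the same amount.

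**The case against.** The strongest reply is that the design is not unprotected and that bias is possible, not shown.

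A reader might infer that nothing guards the comparison. The article does not support that. Physicians are drawn at random for approach, non-responders are followed up, patients are drawn at random and the abstractor is blinded. The invitation is kept vague to weaken selection on interest in diabetes care, which is the trait that would drive an imbalance. These count as partial safeguards. They do not close the gap: random selection protects the list approached, not acceptance; blinding the nurse protects ascertainment; and a vague letter cannot undo the arms' different exposure before it arrives.

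A reader might also infer that the group effect is biased. That requires acceptance to differ by arm and the difference to relate to statin prescribing. Equal self-selection in both arms would limit generalisability without biasing the comparison. Both arms also received the newsletter, so general contact with the association is not differential.

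Three further inferences go beyond the text:

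- That recruiting staff know the arm. The article does not say either way.
- That recruitment comes a year after the mailing. Abstraction starts in spring 2010, but no recruitment date is given.
- That group is the only model term. The article names no other, but the full protocol or analysis plan may.

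The size is open to challenge too. If Toolkit-prompted volunteers sat 0.5 SD above other acceptors (an assumption), a shift of 0.2 to 0.3 SD would need 0.2/0.5 = 40% to 0.3/0.5 = 60% of the intervention physicians, 16 to 24 of 40, to be such volunteers, with none in the control arm. That is demanding for a mailed package. The objection therefore limits the claim to a risk of unknown size. It does not change the order of events: consent follows exposure.

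**Conclusion.** The point holds as a risk. The 80 participants are a consenting subset formed after allocation and after delivery to one arm, so randomisation alone does not protect their comparison, and the stated safeguards address differential acceptance only in part.

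No estimate of the bias is possible from the article. The range of 2.1 to 3.2 points, with rejection of about 10% to 16% under no effect, rests on an assumed shift of 0.2 to 0.3 SD, a one-third statin rate and the plan's intraclass correlation of 0.05. At zero shift the test keeps its 5% level. Because a modest shift approaches one standard error, and the plan already intends to abstract baseline drug use, baseline adjustment is a cheap improvement worth making. Recruiter masking and reporting by arm are details that an article commonly leaves out, so they are secondary.

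**What to change.** Define baseline statin use as the patient's status at the last chart record before the spring 2009 mailing. Include it as a prespecified covariate in the primary multilevel logistic model, both as the patient's value and as the physician's mean. Add a category for no pre-mailing record, to cover patients who are new to the practice or newly diagnosed.

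Cost: the abstractor must date baseline use to before the mailing, and some patients will have no earlier record, because eligibility requires only one visit between July 2009 and March 2010. The variable itself comes from data already planned. The adjustment should also improve precision. It reduces selection bias but cannot remove differences between acceptors that earlier statin use does not capture.

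Secondary, if not already planned: keep the arm code from the staff who fax and telephone, and report the numbers of physicians approached and accepting by arm. Both are administrative changes.

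### Patients are sampled on a post-mailing visit and on undated chart criteria that the Toolkit could influence, so the arms can differ by selection, probably by a modest amount

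*Protocol article*

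**What the plan says.** Under Study participants, 20 diabetic adults per physician are drawn at random from billing or electronic records, from those "who were seen in the office at least once between July 2009 and March 2010, and who fulfill the Clinical Practice Guidelines" definition of high cardiovascular risk. Men from 45 and women from 50 meet that definition by age. Younger patients need at least one further feature: macrovascular or microvascular disease, a family history of premature disease, an extreme LDL-C or systolic pressure, or long diabetes duration.

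Under Data collection and outcomes, the timing is: "Starting in the spring of 2010, we will perform a retrospective data abstraction from the paper charts and/or electronic health records". The outcome window equals the visit window: "Outcome measures will be assessed for each patient for the period between July 2009 and March 2010". No date limit is given for the entries that establish high risk.

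On what the Toolkit is for, the Background states: "The strategy highlighted the identification of diabetic patients at high risk for cardiovascular events, treatment targets and methods for vascular protection". The Intervention section lists a card with "a simplified algorithm for cardiovascular risk assessment, vascular protection strategies and screening for cardiovascular disease", and also "a pad of tear-off sheets for patients with a cardiovascular risk self-assessment tool".

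**The concern.** Practices were randomised, but the patients analysed are picked later, using information that arises after the intervention arm had the Toolkit. One aim of the Toolkit is to have physicians identify high-risk patients and screen for cardiovascular disease, and high-risk status is also an entry criterion. If intervention physicians document more risk features in younger patients, or see patients who would otherwise have stayed away, their 20 sampled patients come from a somewhat different population than the control patients. Randomisation does not protect a comparison of groups formed in that way, and part of any difference in statin use could reflect who was sampled rather than how they were treated.

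**Working it through.** **1. Order of events.** Mailing to the intervention arm: spring 2009. Qualifying visit and outcome window: July 2009 to March 2010. Chart reading and mailing to controls: spring 2010. The visit criterion lies wholly after the mailing. The chart criteria are read about a year after it, with no stated look-back limit.

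**2. What allocation could alter.**
- Age: not alterable. It alone qualifies men from 45 and women from 50.
- Chart features in younger patients: screening could reveal vascular disease. Family history and diabetes duration can change only in how they are recorded. Earlier treatment could keep a patient below the LDL-C or blood pressure threshold. These act in different directions.
- The visit: applies to patients of every age, but requires only one visit in nine months.

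**3. The plan's own figures, for scale.** The stated 408 per group is reproduced by 40% vs 50% (or 50% vs 60%), two-sided 0.05, 80% power, with continuity correction. VIF = 1 + 19 × 0.05 = 1.95; 408 × 1.95 = 795.6, so 796 patients; 795.6/20 = 39.8, so 40 physicians. The target is 10 points.

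**4. Size of a selection effect (all inputs assumed; the article gives none).** Let q be the excess share of the intervention sample present only because of post-mailing entries or visits, and D the statin-rate gap between those patients and the rest. Bias ≈ q × D.
- Chart route: q = (share qualifying only by the younger-age criteria) × (relative rise in identification).
  - Low: 0.05 × 0.10 × 0.20 = 0.001, or 0.1 point.
  - Middle: 0.10 × 0.20 × 0.30 = 0.006, or 0.6 point.
  - High: 0.15 × 0.30 × 0.40 = 0.018, or 1.8 points.
  - The product ignores the enlarged denominator. With it, the high case is 0.045/1.045 × 0.40 = 0.017, or 1.7 points.
- Visit route: 2% to 5% extra patients with statin use 20 points lower. 0.02 × 0.20 = 0.004 and 0.05 × 0.20 = 0.010, or 0.4 to 1.0 point, here lowering the intervention rate.

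**5. Compared with sampling error.** With 800 per arm and a statin rate of one-third (the ceiling quoted for current use), SE = √(2 × 1/3 × 2/3 × 1.95/800) = 0.033, or 3.3 points. Two-sided type I error at nominal 5%, by size of bias:

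| Bias (points) | Type I error |
|---|---|
| 0.6 | 5.4% |
| 1.0 | 6.1% |
| 1.5 | 7.4% |
| 2.0 | 9.3% |
| 3.0 | 14.9% |

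The 3.0-point row needs, for example, q = 10% and D = 30 points. The chart route alone reaches at most q = 0.15 × 0.30 = 4.5% and the visit route 5%, so both would have to be at their extremes.

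**6. Compared with a smaller true effect.** The Discussion cites a review with a median improvement of 4.3 points for categorical process measures. Against that, 0.6 point is 0.6/4.3 = 14% and 1.8 points is 1.8/4.3 = 42%.

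**The case against.** The strongest reply is that few patients can be affected. Most are likely to qualify on age, the Toolkit is not described as finding new cases of diabetes, and no recall or outreach to absent patients is described. A patient with diabetes will probably be seen once in nine months in either arm. Patients are drawn at random, the abstractor is blinded, and baseline drug use and comorbidities are collected, so imbalance can be examined. Finally, a journal article may leave look-back dates to an abstraction manual.

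Much of this stands as a limit on size. It does not remove the point. Random sampling and blinding act on a sampling frame and on charts that were already formed after allocation. The collected covariates make imbalance partly visible but do not prevent it. Silence on a chart cut-off does not prove that none exists; the visit window, however, is stated outright and placed after the mailing.

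A reader might infer more than the article supports:
- That the Toolkit tells physicians to look for and record each listed criterion. The list is the trial's eligibility list. The Toolkit is described only as highlighting identification and as giving an algorithm for risk assessment and screening.
- That the Toolkit brings in otherwise unseen patients. Nothing in the article shows this; it is only possible.
- That the result must favour the Toolkit. The mechanisms pull in different directions.

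**Conclusion.** The point holds as a design weakness of modest likely size. Eligibility rests on a post-mailing visit and on chart criteria with no stated pre-mailing limit, while the Toolkit targets identification of, and screening for, the same risk. The arms can therefore differ by selection; the article does not show that they will.

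The chart route reaches only men under 45 and women under 50. Under the assumed inputs it is worth 0.1 to 1.8 points, about 0.6 in mid-range, against a 10-point target and a standard error of about 3.3 points. The visit route is more speculative. This does not invalidate the trial, but it should be corrected, because the sign is unknown, the bias cannot be called conservative, and the remedy is cheap before abstraction starts.

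**What to change.** In both arms alike:
- Judge diabetes status and the chart-based high-risk criteria only on entries dated before the spring 2009 mailing, and compute age at one common fixed date.
- Draw the 20 patients from those with an office visit in a fixed period before the mailing.
- Report by arm the proportion of these patients seen between July 2009 and March 2010.
- State in advance how those without such a visit are handled: for example, primary analysis in those seen, and a sensitivity analysis counting the unseen as not receiving a statin. This step is needed because analysing only those seen brings the visit-based selection back, while counting the unseen as untreated mixes visit frequency into the outcome. The two together show whether it matters.

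If the sampling frame cannot be changed, add a sensitivity analysis restricted to patients who qualify on age alone and had a pre-mailing visit.

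The cost is mainly a change to the sampling and abstraction instructions. Patients newly diagnosed or newly registered after the mailing are excluded, and some sampled patients will have no visit in the outcome window.
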